#### Criteria for discontinuing allocated interventions for a given trial participant

Generally, both, BLT and EI, are considered as safe interventions with no specific, relevant risk conferred to the trial participants. The BLT device implemented in this study (Chronolux Medic-4) uses UV and infrared (IR) filtered therapeutic light (10,000 lx) and is thus safe for the eyes and skin. If side effects occur (e.g. nausea, headache, eyestrain), they are usually mild and short-lived [81]. In rare circumstances, BLT can trigger a manic episode in bipolar disorder, which is therefore an exclusion criterion [81]. Regarding the EI arm of the intervention, it should be said that the risks associated with exercise are directly related to the “dose” of exercise and top athletes are at a high risk of suffering different types of injuries. However, in this study, the exercise administered will be recreational and only small injuries (e.g. ankle sprain) might occur with a comparable probability to school recess (in the case of adolescent participants) or in any daily activity. If any undesirable effect occurs, this will be reported as an adverse event (AE) and reported to the local primary investigator and to the principal investigator (PI) who will decide about withdrawal of participants from the clinical trial (see Additional file 2). All ongoing AEs/serious adverse events (SAEs) of withdrawn participants will be followed up until no more signs and symptoms are verifiable or the participant is in a stable condition or the participant has taken back his/her approval for medical follow-up.

#### Strategies to improve adherence to intervention protocols and any procedures for monitoring adherence

To ensure comparability of the BLT and EI interventions between the four different centers, detailed manuals have been developed that: provide a standardized psycho-education element to explain the basic elements of the respective therapy and its mode of action; detail the frequency and duration of the respective therapy; detail the m-health-based electronic monitoring, reinforcement, and coaching part; and provide the clinical therapist with standardized motivational interviewing skills to improve participants’ compliance with the intervention. Participants’ compliance with the intervention (BLT and EI) is monitored with the m-health app and the light and activity sensor throughout the ten weeks of intervention. Therapists have no access to this information but will assess participants’ compliance based on interviews at T3.

#### Relevant concomitant care and interventions that are permitted or prohibited during the trial

Psychotropic medication is started or changed at least four weeks before randomization and needs to remain stable (mg/kg body weight) throughout the intervention and the three-month follow-up of the study (with the exception of dose adjustment to body weight changes). The following psychotropic medication is allowed as single or combined treatment: any ADHD-specific medication, antidepressive treatment, and low dose neuroleptic treatment to control aggressive behavior or mood swings. In addition, stable medication for the treatment of chronic conditions as allergies, asthma, enuresis, sleeping problems, and intermitting medication for acute infections or pain is allowed. Pharmacological treatment is documented at each time of assessment (T1–T5, see Fig. 3) and psychotropic medication effects on treatment outcome will be explored in analyzing study outcomes. Any individual-based (e.g. CBT that does not include elements of BLT and EI, school-based intervention, occupational, language, psychomotor therapy) as well as family-based intervention is allowed. Any additional treatment is documented exactly (kind of intervention, frequency, etc.). The following concomitant treatments are not permitted during the trial: additional EI and additional BLT. Relevant additional treatments administered to the participants on entry to the trial or at any time during the trial are regarded as concomitant treatments and are documented on the appropriate pages of the case report form (CRF).

### Outcome measures

The primary outcome measure is the change in the clinician-rated Inventory of Depressive Symptomatology (IDS-C_30_) [82] total score (observer-blinded assessment) between baseline (T2) and after the end of the intervention (T4, primary endpoint, see Fig. 3). The IDS-C_30_ rating includes all DSM-5 diagnostic criterion items for major depressive disorder (e.g. mood, vegetative, psychomotor, and cognitive symptoms) as well as commonly associated symptoms such as anxiety, irritability, melancholic, and atypical symptom features to assess the severity of depressive symptoms over the last seven days. Items are rated on a 4-point Likert scale based on the information obtained during a semi-structured interview. The total score range is 0–84. The psychometric properties of the IDS-C_30_ and its sensitivity to change with interventions have been well established in different study samples and RCTs [82–84]. Parallel versions exist in English, German, Spanish, and Dutch. The IDS is under investigation in adolescent patients; however, a standardization for individuals aged 14–17 years is still lacking. Because changes in raw scores are assessed in this study, the IDS-C_30_ is considered a valid measure in adolescents.

The secondary outcome measures aim to assess intervention effects on depressive symptoms at the 12-week follow-up (T5) and to differentially assess changes in obesity, health-related quality of life, ADHD symptoms, general psychopathology, chronotype, neurocognitive function, body-related measures, and physical fitness between baseline (T2), the end of intervention/ TAU (T4), and 12-week follow-up (T5). In addition, secondary outcome measures include several parameters measured with the m-health app between the one-week baseline and one-week post-intervention assessment. Also, hormone concentrations will be assessed in a Frankfurt subsample at T2 and T4. All scales and questionnaires as well as physical fitness tests and neurocognitive tests have been frequently used in clinical and non-clinical research and have been validated in adults and mostly also in adolescents (see Additional file 3). For all assessments, parallel versions exist in the languages of the four study sites. Secondary outcome measures are described in detail in Additional file 3.

### Participant timeline

The trial time flow is shown in Figs. 2 and 3. At T1, the diagnosis of ADHD is established by performing structured clinical interviews. The Kiddie-Schedule for Affective Disorders and Schizophrenia - Present and Lifetime Version (K-SADS-PL) [85] is used to assess ADHD symptoms and co-morbid conditions in adolescents. To obtain as much information as possible for high valid diagnoses, both with regard to externalizing and internalizing conditions, the K-SADS-PL will be conducted separately with the adolescent and at least one primary caregiver. For the final rating, the trained clinician will take both sources of information into account. In adults, the Diagnostic Interview for ADHD in adults (DIVA) [86] is administered to assess ADHD symptoms and the Structured Clinical Interview for DSM-IV Axis I and II Disorders (SCID-I and II) [87] to assess co-morbid conditions. The Adult ADHD Self-Report Scale (ASRS) [88] and the Wender-Reimherr Adult ADHD Symptom Rating Scale (WRAADDS) [89] are used to substantiate diagnosis. All interviews and questionnaires will be adjusted to DSM-5 criteria. After having established the diagnosis of ADHD and having completed screening for eligibility based on interviews/questionnaires (Alcohol Use Identification Test [AUDIT] [90], National Institute on Drug Abuse [NIDA] Quick Screen [91], Physical Activity Readiness Questionnaire [PAR-Q] [92], physical examination, and IQ tests [Wechsler Adult Intelligence Scale, WAIS-IV [93]/ Wechsler Intelligence Scale for Children, WISC-IV [94]], informed consent is obtained. Trial-specific assessments are done at T1 after informed consent has been obtained and m-health will be introduced to participants and their parents (if applicable) (T1, duration = approximately 5 h for adults and 3.5 h for children/parents including breaks). Within two weeks after T1, the one-week baseline assessment with the m-Health system takes place at home. During this week, participants will wear the light and movement sensors on two working days and on Saturday and Sunday (always 24 h) and they will be asked to answer questionnaires (regarding mood regulation, reward and stress reactivity, sleep behavior, inattention, and context) 12 times a day (duration = 1 min each) provided by the m-health app. A subset of adult participants from Frankfurt are also asked to collect saliva on one day of the one-week period at home ten times over 24 h (immediately after awakening: approximately at 07:00, 30 min after wakening: approximately at 7:30 am, 11.00 am, 6.00 pm, 7.00 pm, 8.00 pm, 9.00 pm, 10.00 pm, midnight, 1.00 am) by chewing on a cotton swab which will be stored in tubes (Salivette™, Sarstedt, Germany). All participants are asked to fill out several questionnaires on the last day of the one-week period (duration = approximately 1 h) and to bring them along at T2. Baseline assessment based on interviews, questionnaires, body parameters/ fitness tests, and neurocognitive tests will be finished at T2 (duration = approximately 4 h for adults and children/parents including breaks) which is scheduled within three weeks after T1 and within one working week after the one-week m-health baseline assessment. Thus, all primary and secondary outcome measures are obtained either at T1, T2, or during the one-week baseline assessment. The randomization takes place at T2. Participants will be instructed in how to use the m-health app for the respective therapy and they will be introduced to all devices. Experimental groups will begin with the interventions the next day, while the control group continues with TAU which lasts for ten weeks. One week after T2, participants will be contacted via email to administer the Rey Auditory Verbal Learning Test (RAVLT) [95] recognition subtest (by sending a link via email to an online survey, 10 min). T3 (mid-intervention assessment) will take place five weeks after T2 (± 3 days). This mid-intervention assessment aims at obtaining the primary and secondary outcome measures during the ongoing trial to get some information on participants dropping out from the study before T4 (duration of T3 = approximately 3 h for adults and children/parents including breaks). Experimental groups will continue with the interventions for another five weeks while the control group continues with TAU. After ten weeks of intervention or TAU (control group) (five weeks after T3 ± 3 days), primary and secondary outcome measures are assessed again (duration = approximately 4 h for adults and children/parents including breaks), followed by a one-week post-intervention assessment with the m-health system including the same parameters as during the baseline m-health assessment. Saliva will be taken during one day of the one-week period (using the same procedure as during the baseline assessment) in the Frankfurt subgroup. One week after T4, participants will be contacted via email to administer the RAVLT recognition subtest. To assess the stability of the therapy effects, the study also includes a follow-up (T5) assessment 12–14 weeks after T4 (T5, duration = approximately 4 h for adults and children/parents including breaks). One week after T5, participants will be contacted via email to administer the RAVLT recognition subtest.

**Fig. 2 Fig2:**
[figure not shown]
Trial time flow. T, time-point; I, intervention; EI, exercise intervention; BLT, bright light therapy; TAU, treatment as usual

**Fig. 3 Fig3:**
[figure not shown]
Schedule of enrolment, interventions, and assessments at the different time-points (T1–T5)

### Sample size calculation

The sample size calculation refers to the primary endpoint, more precisely, the expected change in the clinician-rated observer-blinded IDS-C_30_ total score between T2 and T4 in the intention-to-treat (ITT) population. The sample size calculation is based on the expectation to find a clinically relevant medium effect size (d = 0.5) with a two-sample t-test of at least one of the two interventions compared to TAU on the primary endpoint. As this is a pilot study to establish effect sizes, the sample size is planned at the liberal significance level of α = 0.10 (two-sided) and the power of 1-β = 80%. Taking into consideration the three-group design and an expected drop-out rate of about 30%, n = 219 participants will be allocated and analyzed. Based on the information received from the clinical study centers, it is expected that about 25–35% of the screened participants cannot be included in the study due to violation of inclusion/exclusion criteria. Hence, n = 330 participants will be assessed for eligibility. It can be expected that application of an analysis of covariance in the evaluation will reduce the standard deviation thus increasing the actual power of the study. Sample size calculation was done using ADDPLAN v6.1 [96].

### Recruitment

Recruitment and treatment of participants will be provided at four trial centers, each enrolling 55 participants. King’s College is affiliated with a number of National Health Service foundation trusts across England. The other clinical centers are affiliated or part of University Hospitals and have large outpatient units specialized in ADHD diagnosis and treatment across the life-span, so that the planned recruitment numbers are feasible. Participants are recruited by flyers, public notices, and personal contact from inpatient and outpatient departments of the participating sites, as well as by public announcements, press releases, newspaper advertisements, and Internet/social media campaigns. Measures are in place to mitigate risk in the case of under-recruitment: reimbursement to individual centers will be done in the form of case payment, as stipulated in an agreement before beginning of the trial; pre-financing is carried out on an annual basis. In the case of a participating site falling short of the recruitment plan, the CoCA (EU project Comorbid Conditions of Attention deficit / hyperactivity disorders) steering committee, advised by an independent Data Safety and Monitoring Board (DSMB, see below), reserves the right to stop study participation for this site and either increase recruitment numbers at the remaining sites or include a new recruitment site.

### Assignment of interventions

After written informed consent, participants are successively randomized to one of the three groups (BLT, EI, TAU). At each center, the trial coordinator generates the randomization code using a centralized web-based tool [97] which will be done at T2 after all baseline measurements have been completed in order to ensure allocation concealment. Randomization is a block randomization per center and is done in an allocation ratio of 1:1:1 with fixed block length and stratified for each participating center. The randomization list will be kept in safe and confidential custody at the Institute of Medical Biometry and Informatics (IMBI). Participants withdrawn from the trial will retain their identification codes (e.g. screening number, if already given). New participants must always be allocated a new identification code. As the proposed study is a non-pharmacological therapy intervention study, blinding of participants as well as therapists is not possible. However, the design is observer-blinded. Clinicians, who assess the primary outcome measure, the IDS-C30 total score, and the ADHD Rating Scale total score, are blind to treatment allocation. Therefore, at each site, randomization will be done only by the trial coordinator who is also the only person who will manage the investigator site file (ISF). Clinicians are not involved in the randomization procedure and are not allowed to receive information about group assignment. Clinicians will be provided with data recording sheets and data will be entered into the CRF by the trial coordinator. In addition, participants are instructed not to talk about their intervention at each visit. Adherence to randomization is monitored by an independent clinical on-site monitor, the Coordination Centre for Clinical Trials (KKS), University Hospital Heidelberg.

### Data collection methods

#### Training plans

Group training sessions for all psychologists/psychiatrists involved in the trial from all centers took place at several consortium and kick-off meetings before the trial start. Trainings covered study requirements (e.g. observer-blinded assessment of the primary outcome measure), general information about obtaining research quality data, and recording data (e.g. discussing data collection forms in detail on an item-by-item basis). Data collection forms and the standard operating procedures (SOPs) can be downloaded from the CoCA intranet. The data to be collected and the procedures to be conducted at each visit will be reviewed in detail (see data management and monitoring). Furthermore, intervention manuals were discussed in detail at previous meetings and phone conferences. At subsequent CoCA consortium meetings and during regular monthly phone conferences, clinicians will be monitored with regard to the correct implementation of the manuals and evolving questions can be discussed and solved. The training sessions also included training of the standardized procedures to assess primary and secondary outcome measures. Reliability training of the primary outcome measure will be continued locally following a standard procedure and inter-rater reliability will be assessed during the course of the trial.

#### Participant retention

Once a participant is enrolled or randomized, the study site will make every reasonable effort to follow the participant for the entire study period. Study site staff are responsible for developing and implementing local SOPs to achieve a low rate of loss to follow-up (e.g. reminding participants and parents of the upcoming visits via phone call or email, motivational interviews during visits, etc.).

#### Participant withdrawal

Participants may either withdraw themselves from the intervention, but will stay in the study (I) or the participants may totally withdraw from the trial (II). A third option is that, due to SAEs or other events, the PI decides that the participant has to withdraw from the study. Participants withdrawing at their own request or at request of their legal representative: participants and their legal representatives are allowed to withdraw their consent to participate in the study and the study interventions at any time. The data which were collected before the withdrawal will be used in the statistical analysis. If an individual or the legal representative totally withdraws from the trial and requests the extinction of data, the data cannot be included in the statistical analysis and will be erased from the database. The PI or the local primary investigator needs to decide on the participant’s study withdrawal in the following situations: (i) if, in the principal or primary investigator’s opinion, continuation of the treatment would be detrimental to the participant’s wellbeing; (ii) with admission into a psychiatric hospital; (iii) new occurrence of exclusion criteria under the condition that the security of the participant is thereby endangered. A change in pharmacotherapy is no criterion for withdrawal from the trial. The principal or the local primary investigator decides about withdrawal of participants from the clinical trial or from the investigation in case of occurrence of the criteria mentioned above.

A very low frequency of AEs/SAEs can be expected for BLT and EI. Nevertheless, a DSMB will be installed and safety-relevant events will be reported to this board. Based on the recommendations of the DSMB, the study might be stopped. In all cases, the reason for withdrawal will be recorded in the CRF and in the participant’s medical records. In case of withdrawal of an individual at his/her own request, as far as possible the reason will be asked for as extensively as possible, and documented.

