### Statistical methods

#### Primary outcome

Statistical methods are used to assess the quality of data, the homogeneity of the treatment groups, the efficacy endpoints, and the safety of the three treatment groups. The confirmatory analysis of the primary endpoint will be conducted on the basis of the ITT population. An additional analysis will be conducted for the per-protocol (PP) population that includes all participants without major protocol violations.

A closed testing procedure will be applied controlling the overall type I error rate at 0.05 (two-sided). A mixed model for repeated measures (MMRM) approach investigating the treatment effect with respect to all three intervention groups will be used. Two-group comparisons I-1 vs TAU, I-2 vs TAU, and I-1 vs I-2 based on contrasts will follow. Baseline IDS-C_30_, age, IQ, sex, treatment, and center will be included as covariates. The MMRM approach models jointly all actual observations without imputing missing data but using the within-participant correlation structure to provide information about unobserved post-baseline primary endpoints. Gender effects are of particular interest. If there are not enough events per category for the different covariates, gender effects will be excluded from the MMRM analysis and investigated in a secondary analysis. The MMRM approach, by which the missing values with respect to post-baseline primary outcomes are dealt with, demonstrates favorable characteristics in terms of type I error rate, power, and bias of estimates compared to alternative methods dealing with missing values, such as last-observation-carried-forward (LOCF) [98–100].

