#### Additional analyses

Descriptive methods will be used for the analysis of the secondary outcomes, including the calculation of appropriate summary measures of the empirical distribution (mean, standard deviation, median, minimum and maximum for continuous variables, and frequency in percentages for categorical variables) as well as calculation of descriptive two-sided *p* values. A special focus of the exploratory analysis will be with respect to the time course of the primary as well as the secondary endpoints. Additionally, sensitivity analyses will be conducted for different populations (PP population, appropriate subgroups) and applying different imputation techniques (such as LOCF) for missing values. Further exploratory analyses will be performed to identify intervention effects in subgroups and potential prognostic factors (including hormone levels) for an intervention effect. Furthermore, variables possibly mediating treatment effects such as reward processing, stress reactivity, and compliance with the interventions will be explored. Appropriate regression will be used following the four-step procedure by Baron and Kenny [101]. Graphical methods will be applied to visualize the findings of the study. The safety analysis will be based on the set of all randomized participants who were exposed to study intervention at least once and includes calculation and comparison of frequencies and rates of adverse and serious adverse events reported in the two intervention groups. All analyses will be done using SAS version 9.4 or higher. A statistical analysis plan will be written before the final analysis.

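### The withdrawal rule can end IDS-C30 collection at psychiatric admission, an event plausibly related to the primary outcome, and conflicts with the retention commitment

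*Protocol article*

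**What the plan says.** All references are to the protocol article.

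- **Participant withdrawal, participant's own choice.** Two forms are described. The first keeps the participant under observation: "Participants may either withdraw themselves from the intervention, but will stay in the study (I"). The second is total withdrawal from the trial.
- **Participant withdrawal, investigator's choice.** A third option is that "due to SAEs or other events, the PI decides that the participant has to withdraw from the study". The principal or local primary investigator "needs to decide on the participant’s study withdrawal in the following situations". The situations are: continuing would harm the participant; psychiatric admission ("with admission into a psychiatric hospital"); and a newly arising exclusion criterion, but only if the participant's safety is thereby at risk. Acute suicidal ideation is one of the exclusion criteria in Table 1.
- **Closing sentence of the rule.** The investigator "decides about withdrawal of participants from the clinical trial or from the investigation in case of occurrence of the criteria mentioned above". The difference between the two objects of withdrawal is not explained.
- **Data use.** "The data which were collected before the withdrawal will be used in the statistical analysis". This stands in the text on withdrawal at the participant's own request. Nothing says whether ratings continue after an investigator's decision. Reasons for withdrawal are always recorded.
- **Participant retention.** Sites are to try to follow each enrolled or randomized participant to the end of the study.
- **Primary outcome and Additional analyses.** The confirmatory analysis is an MMRM in the ITT population without imputation. Sensitivity analyses include "applying different imputation techniques (such as LOCF) for missing values".

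**The concern.** The endpoint is change in depressive symptoms from T2 to T4. Psychiatric admission and newly arising suicidal ideation are events that a high IDS-C30 score could plausibly accompany or precede. If the score stops being collected at that point, it is missing because of what it would have shown.

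The MMRM is valid when missingness depends only on what has been observed (baseline, T3 and covariates). A deterioration after the last rating that also ends rating breaks that condition. The participant's T4 value is then in effect predicted from people who did not deteriorate. LOCF does not expose this, because it carries forward a score from before the deterioration.

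In the TAU arm there is no trial intervention to stop, so study withdrawal there mainly ends outcome collection. At stake is the ITT contrast at T4. It would be pulled towards zero if more TAU participants are lost this way, and would flatter the intervention if more active-arm participants are.

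**Working it through.** **1. The plan's own figures.** Inputs from Sample size calculation: d = 0.5, two-sided α = 0.10, power 80%, three arms, about 30% drop-out. The two-sample t-test needs 51 per arm (power 0.806; 50 per arm gives 0.799). Then 3 × 51 = 153, and 153 / (1 − 0.30) = 218.6, so 219 in total or 73 per arm. This reproduces the stated 219. With 51 per arm and α = 0.05 the power is 0.706, in line with the 70% stated under Primary outcome. The plan therefore allows for 0.30 × 73 ≈ 22 participants per arm without a T4 score, for any reason. It does not say how many of these would be admissions.

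**2. Does the text end outcome collection?** Side by side:

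- Participant's own choice: two routes, one of which expressly keeps the person in the study.
- Investigator's choice: withdrawal from the study, then a closing sentence with a second, undefined possibility.
- Participant retention: follow-up to the end for everyone randomized.
- Criteria for discontinuing allocated interventions: ongoing adverse events of withdrawn participants are still followed up, so contact for safety continues.
- Participant withdrawal: a change in pharmacotherapy is not a reason to withdraw, so treatment changes after randomization are accepted elsewhere.

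A site could end IDS-C30 rating at admission and be following one section, or continue it and be following another.

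**3. Size of the bias in the T4 contrast.** Let p be the share of an arm whose T4 score is lost through this rule. Let s be how much worse, in SD, those unseen scores are than the MMRM predicts from baseline and any T3 score. Then

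bias ≈ p(TAU) × s(TAU) − p(active) × s(active),

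which for equal s becomes (difference in p) × s. The documents give neither p nor s, so both are assumptions:

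| Difference in p | s = 1 SD | s = 1.5 SD | s = 2 SD |
|---|---|---|---|
| 2% (about 1.5 of 73) | 0.02 | 0.03 | 0.04 |
| 5% (about 3.7 of 73) | 0.05 | 0.075 | 0.10 |

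Relative to d = 0.5: 0.02 / 0.5 = 4% at the low end and 0.10 / 0.5 = 20% at the high end. If p and s are the same in both arms, the contrast is biased by about zero, although each arm's mean is still too favorable (for example by 0.05 × 1 = 0.05 SD at p = 5% and s = 1).

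**The case against.** The strongest reply is that the rule is discretionary and the text leaves room. The investigator decides; admission does not remove anyone automatically. The closing sentence may be meant to allow withdrawal from the intervention alone. The sentence limiting data use to what was collected earlier belongs to withdrawal at the participant's own request. New exclusion criteria count only if safety is endangered. Reasons are recorded, T3 is there partly to inform on people who leave before T4, and the MMRM uses T3. All of this stands and limits the point. It does not settle whether rating continues, because the second possibility is undefined and the only route that expressly keeps someone in the study is the self-chosen one.

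Several stronger readings are tempting, and the documents do not support them:

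- **That the expected 30% drop-out consists largely of such cases.** It is all-cause, and no admission rate is given. Severe co-morbidity needing inpatient or day care, and acute suicidal ideation, are excluded at entry, so admissions are probably far fewer.
- **That the effect would shrink to 0.7 × 0.5 = 0.35.** That figure assumes every active-arm drop-out ends like TAU. It is a different assumption about all drop-outs, not a bias caused by this rule.
- **That the decision is made unblinded.** Assignment of interventions says participants and therapists cannot be blinded and rating clinicians are. It does not give the status of the investigators who decide.
- **That naming LOCF is an error.** It is an example in an open list of sensitivity analyses beside a primary MMRM. The statistical analysis plan, not shown, may add others.

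**Conclusion.** The point holds as a defect in the withdrawal rule. As written, the rule allows outcome collection to end at an event plausibly related to the outcome, does not define its two forms of withdrawal, and conflicts with the retention section and the ITT aim. A later analysis plan cannot recover T4 scores that were never collected, which is why it matters at protocol stage.

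The size is uncertain and probably modest: about 0.02–0.10 SD (4–20% of d = 0.5) under assumed between-arm differences of 2–5% and shifts of 1–2 SD, and about zero in the contrast if the arms are alike. The direction depends on which arm loses more participants this way. It should be corrected, but it does not invalidate the design. The choice of example for the sensitivity analyses is a secondary matter.

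**What to change.** **Main change.** Reconcile Participant withdrawal with Participant retention. State that an investigator's decision about the intervention does not by itself end outcome collection, and that the remaining IDS-C30 ratings (T3, T4, T5) are still sought unless consent is withdrawn. Define what withdrawal from the trial and withdrawal from the investigation each mean for data collection. The clinical decision, and the situations that prompt it, are left as they are.

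**Secondary change.** In Additional analyses, name a delta-adjusted or reference-based analysis of the T4 IDS-C30, using the recorded reasons for withdrawal, instead of LOCF as the example. Such analyses examine departures from missing at random; LOCF does not.

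**Cost.** A protocol clarification, a few extra ratings and some programming. The downside is that scores retained after admission include the effect of post-admission care. That is consistent with an ITT comparison but should be said when results are reported.
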